### Study period

The study will run for 16 months in each ward. We will stagger the start date for each trust, and for different wards in each participating trust, to allow effective management of the patient recruitment process.

### Outcome measures

The PRASE intervention wards receive patient feedback directly relevant to their area, and then identify areas for improvement and plan targeted changes on the basis of the areas identified. The lack of a focus on a specific safety outcome means that more generic measures of safety are necessary.

#### Primary outcome measures will be

Patient Safety Thermometer data. These are routinely collected hospital ward level data which all wards in England are mandated to collect on a monthly basis. It collects data about:pressure ulcersnewly acquired venous thromboembolismscatheter associated Urinary Tract Infectionsfalls

An overall measure of harm-free care is then calculated per ward. The outcome can range between 0 and 100, with higher scores indicating a higher percentage of harm-free care.2)PMOS questionnaire domain scores. The 44-item questionnaire is scored into nine domains and one single item.

#### Secondary outcome measures

Three Commissioning for Quality and Innovation questions (from patients, at the end of the questionnaire) which are:Were you involved as much as you wanted to be in decisions about your care and treatment? (Yes, definitely/Yes, to some extent/No)Did you find someone on the hospital staff to talk to about your worries and fears? (Yes, definitely/Yes, to some extent/No/I had no worries or fears)Were you given enough privacy when discussing your condition or treatment? (Yes, always/Yes, sometimes/No).

Each question will be considered separately with the proportion of patients responding in the ‘Yes’ categories combined for analysis purposes.2)Family & Friends question, which is: ‘How likely are you to recommend this ward to friends and family if they needed similar care or treatment?’

Patients can respond on a 5-point Likert scale (extremely likely, likely, neither likely nor unlikely, unlikely, extremely unlikely). The proportion reporting ‘Extremely likely’ and ‘likely’ will be used in the analysis.3)Staff safety culture (Additional file 1: Appendix 5), including:Ten questions from NHS national annual staff survey included items pertaining to ‘working on the ward’, ‘staff contribution to patients’, and ‘improving work practices’.Four questions from the Hospital Survey of Patient Safety regardingperceptions of patient safety (mean of 4 items, ranging from 1.0 to 5.0 with 1 representing a low score and 5 representing a high score)frequency of event reporting (mean of 3 items, ranging from 1.0 to 5.0 with 1 representing a low score and 5 representing a high score)number of events reported in the last 12 months (1 item, categorical scale)a ward patient safety grade from 1 to 5 (1 = excellent, 5 = failing).

We will also seek to access from the trusts some routinely collected ward-level data from participating wards:Patient safety incidents for the study period will be collected using standard incident reporting by staff to the regulatory authorities. Standard reporting of patient safety incidents will be categorised into harm and no harm events.Complaints and comments reported to NHS Patient Advice Liaison Service (as a secondary outcome)Ward level covariates (staff absence/sickness rates, nurse/patient ratios and number of discharges per month) will also be collected for exploration in the analysis.

These data will be collected at baseline, 6 months and 12 months apart from the Staff Safety Culture which will be collected at baseline and 12 months.

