### Setting and sample

This study will be undertaken within 32 hospital wards, spread across three NHS Trusts, over five different hospital sites (eight wards at a small district general hospital, 10 wards at a medium sized teaching hospital and 14 wards at a very large teaching hospital). Study participants will be patients within participating wards. An average of 25 patients within each ward will be recruited at three different time points across the study period. Each time point lasts 3 to 4 weeks and data collection occurs within the same 3- to 4-week window for all participating wards in the same Trust. The eligibility criteria for the study are given below but, briefly, the selection criteria for participation is: any patient aged 16 years or over who has capacity to give informed consent to take part. All patients who satisfy the eligibility criteria are approached and then if they agree to take part in the study and give informed consent then they are recruited into the study. Therefore, selection bias is minimal as researchers approach every patient on the ward in a stepwise fashion, unless the patient does not have mental capacity to give informed consent or they are so gravely ill or distressed to the extent that it would preclude the researcher undertaking the PMOS questionnaire with them. Recruitment of patients on a ward ceases when 25 patients have been recruited. The study will involve 800 patients at each time point and equates to a total sample of 2,400 patients. While study participants are patients, the outcome measures are at ward-level meaning that the unit of analysis is the ward.

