### Estimate of sample size

The study will be powered to detect a small to medium difference (effect size = 0.3) between the intervention and control groups with respect to the Patient Safety Thermometer score (See Outcome Measures for explanation of this score). A small to medium effect size seems a reasonable assumption as each ward will be focussing on developing and implementing their own action plans, tailored using their initial feedback. The intervention is therefore specific to individual wards and may not impact on all areas measured by the Patient Safety Thermometer. In order to achieve 80% power (with alpha = 0.05) with an average cluster size of 25 patients and assumed ICC of 0.05, 32 wards will be required (16 per arm). This estimate of ICC seems reasonable for a trial in secondary care with a patient reported outcome
[39].

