Secondary outcomes will be analysed using similar models to the primary outcomes. Ward level covariates will be added to the primary model in order to explore their influence. Continuous measures will be compared between groups using multi-level regression modelling accounting for trust/ward where required and the minimisation factors. Categorical measures will be compared between groups using logistic regression (or ordinal logistic regression for ordinal measures) adjusting for the Trust/ward where required and minimisation factors. The validity and reliability of the PMOS and domain scores will be investigated in this population using Cronbach’s alpha and known-group comparisons. All primary and secondary outcome measures will be summarised at each time point and by intervention group using summary tables or graphs/bar charts depending on the type of data.

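### One 'Yes' scoring rule covers all three CQUIN questions, but only the worries-and-fears question has a not-applicable answer, which as written is scored like 'No'

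*Protocol article*

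**What the plan says.** In the Protocol article, Secondary outcome measures, item 1 lists three patient questions. The question on involvement in decisions offers "Yes, definitely/Yes, to some extent/No", and the privacy question also has two Yes answers and one No. The remaining question, "Did you find someone on the hospital staff to talk to about your worries and fears", offers "Yes, definitely/Yes, to some extent/No/I had no worries or fears". It is the only one of the three with an answer meaning that the question did not apply.

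A single scoring sentence then covers all three: "Each question will be considered separately with the proportion of patients responding in the ‘Yes’ categories combined for analysis purposes". It names patients as the base of the proportion. It neither excludes the fourth answer nor scores it separately.

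The Trial analysis section adds only the model: "Categorical measures will be compared between groups using logistic regression (or ordinal logistic regression for ordinal measures", with adjustment for Trust or ward where required and for the minimisation factors. It does not mention the fourth answer, and neither does any other part of the article.

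**The concern.** The rule suits the two questions with three answers, where every non-Yes is a No. On the worries-and-fears question a non-Yes can mean two very different things: the patient was worried and found nobody, or the patient was not worried at all. Pooling them makes the outcome a product of two quantities: the share of patients with worries, and the share of worried patients who found someone. The question is about the second.

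The intervention aims to improve safety and the patient experience, so a fall in the share with worries is a plausible benefit. The rule gives no credit for that benefit and may count part of it against the intervention. A true improvement in staff response is also spread over patients to whom the question did not apply, so it looks smaller and is harder to detect.

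**Working it through.** **Inputs from the article.** Setting and sample: "The study will involve 800 patients at each time point", so 400 per arm at 1:1. Estimate of sample size: "small to medium difference (effect size = 0.3" and "80% power (with alpha = 0.05) with an average cluster size of 25 patients and assumed ICC of 0.05, 32 wards will be required".

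**Inputs assumed.** The article gives no response split for this question. I take 35% no-worries answers in the control arm (range 20–50%) and 70% Yes among the worried. I borrow the ICC of 0.05, which was set for another outcome, and assume a two-sided 5% test.

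**The plan's own figure.** Per arm, 2 × (1.96 + 0.84)² / 0.3² ≈ 175. The design effect is 1 + 24 × 0.05 = 2.2. Then 175 × 2.2 = 385, and 385 / 25 = 15.4, rounded up to 16 wards per arm, or 32. The figure reproduces. It concerns a different outcome and is used here only to confirm the 2.2.

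**The rule in symbols.** Let w be the share with worries and s the share of worried patients answering Yes. Scored over all patients the outcome is w × s; scored over worried patients it is s.

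**(a) Fewer worries, staff response unchanged.** No-worries rises from 35% to 45%, s = 0.70.
- Control: 0.65 × 0.70 = 0.455. Intervention: 0.55 × 0.70 = 0.385. Difference −7 points.
- SE = √[2.2 × (0.455 × 0.545 + 0.385 × 0.615) / 400] = 0.0516, so z = −1.36.
- Chance of an adverse point estimate: Φ(1.36) = 0.91 (0.91–0.93 over the range).
- Chance of a significant adverse result: Φ(1.36 − 1.96) = 0.27 (0.27–0.30 over the range).

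More generally, a 10-point fall in w at constant s changes the score by −0.10 × s, which is −6 to −9 points for s from 0.6 to 0.9.

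**(b) Better staff response, worries unchanged.** s rises from 0.70 to 0.80 with no-worries at 35%.
- All patients: 0.455 to 0.520, +6.5 points, z = 1.24, power 24% (17–35% over the range).
- Worried only: 400 × 0.65 = 260 per arm, 25 × 0.65 = 16.25 per ward, design effect 1 + 15.25 × 0.05 = 1.76. 0.70 to 0.80, +10 points, z = 2.00, power 51% (46–56%).
- 'No' among all: 0.65 × 0.30 = 0.195 to 0.65 × 0.20 = 0.130, z = 1.69 in the favourable direction, power 39%.

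**(c) Both improve.** 0.65 × 0.70 = 0.455 to 0.55 × 0.80 = 0.440, −1.5 points (0 to −3 over the range).

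**Who loses their worries matters.** Take 100 control patients: 70 worried, of whom 56 answer Yes and 14 No. In the intervention arm, 10 of the 70 are no longer worried.

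| The 10 would otherwise have answered | Yes / all | Yes / worried | No / all |
|---|---|---|---|
| Control arm | 56% | 56/70 = 80% | 14% |
| All No | 56% | 56/60 = 93% | 4% |
| 8 Yes, 2 No | 48% | 48/60 = 80% | 12% |
| All Yes | 46% | 46/60 = 77% | 14% |

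The rule as written is flat or falls in every row, although nobody is worse off. The worried-only proportion can also fall, in the last row. 'No' among all respondents never moves the wrong way here, but it cannot separate fewer worries from better response.

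**The case against.** The article never says in words that a no-worries answer equals No. Its sentence fixes the numerator, and the denominator has to be read from the word 'patients'. A full statistical analysis plan is promised before any analysis, and handling of a not-applicable answer often sits there. This stands in part: that plan may exclude these answers, and this review cannot see it. But the article does not defer the point. It states a rule and applies it to an item it does not fit, and a plan that did otherwise would depart from the published rule.

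A reader might go further and infer that any intervention that reduces worries will lower this outcome and look harmful. The documents do not support that. The score falls only if some patients who lose their worries would otherwise have answered Yes; if all would have answered No, it stays flat. The article reports neither the response split nor any expected effect on worries. The 91% is also easy to over-read: it is the chance that the point estimate lands on the adverse side, not the chance of a significant adverse finding.

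The worried-only denominator is not a clean remedy either. Having worries is a state reported after allocation, and the table shows 80% falling to 77% with nobody worse off. This objection stands in full and shapes the fix.

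Finally, the Trial analysis section promises summaries of all secondary outcomes by group and time point, where the no-worries share might appear. It does not commit to a breakdown by answer category.

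**Conclusion.** The concern holds as a rule that misfits one item. Followed as written, the worries-and-fears outcome measures the share worried times the share of the worried who found someone. Under the assumed split, a true 10-point gain in staff response shows as 6.5 points, with power of about 24% against 51% among worried patients. A 10-point rise in no-worries answers shows as a 7-point loss, with about a 27% chance of a significant adverse result. When both improve, the two gains roughly cancel. The damage is therefore mainly to the size and direction of the estimate, not to the rate of false claims of harm.

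All these sizes rest on the assumed response split, on staff response staying constant among the remaining worried patients in (a), and on the borrowed ICC. The structural point rests on the wording alone. It touches one of three CQUIN questions, a secondary outcome. The primary outcomes and the sample size are unaffected.

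**What to change.** In Secondary outcome measures, add that for the worries-and-fears question the no-worries answer is not scored as a non-Yes. Then report three figures by arm:

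1. Yes (both categories) among patients who gave either Yes answer or No.
2. The share giving the no-worries answer.
3. The proportion answering No among all respondents, with the same standing as the first figure, because it does not condition on a state that the intervention may change.

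If the statistical analysis plan already handles this answer differently from the article, the two texts should be reconciled.

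The cost is a sentence or two of wording and one extra comparison. No new data are needed, since the answer is already collected at every time point. The downside is that the first figure has a smaller denominator (260 instead of 400 per arm at 35% no-worries), restricted on an answer given after allocation; the third figure is there for that reason. Settling this before analysis also removes a later choice between denominators that can give opposite signs.

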### Management of the intervention

The agreement of senior management at the three NHS Trusts (at CEO, Chief Nurse or Medical Director level) has already been gained and participating wards identified. On the basis of previous work undertaken by our team, we realise it is important to get both ‘top-down’ agreement as well as ‘bottom-up’ engagement with ward staff, in order to secure the time, resources and motivation required to participate in such an intervention. To this end, within each participating trust, we will run a series of three, 2-h group ‘Trust debrief’ sessions with the identified APTs from the trust. The first will be a ‘start-up session’, which will run after the first phase of data collection has commenced but before any action planning meetings have begun. The primary purpose of this meeting will be to provide a more detailed briefing about the PRASE intervention, its conceptual basis, how it will work, and what is required of the APTs. A secondary purpose of this meeting will be to bring together all of the intervention wards, to identify potential barriers to the action planning process and share ideas about how best to manage them. The second meeting will be at 6 months. This ‘mid-point’ meeting will be to receive updates from each of the APTs about progress, share their success as well as trouble-shoot any problems, elicit support from senior management where interventions require resources and generally try to maintain motivation for the intervention and the study. The final ‘closing’ meeting will be for the APTs to share their experience of PRASE, discuss changes they have implemented, and allow the research team to gain contextual information about the ward which may affect the outcome measures (see process evaluation section below). Where these debriefing sessions sit in the timeframe of the trial is detailed in Additional file
1: Appendix 4.

### Recruitment and informed consent

Patients will be recruited by researchers from Bradford Teaching Hospitals NHS Foundation Trust alongside research nurses employed by the Trust in which they are collecting the data. A 1-day training course will be given to research nurses external to the core research team. Researchers will liaise with nursing staff on each ward to identify patients who have capacity and are considered well enough to take part in the research. Researchers will then approach appropriate patients to give them information about the study, both written (in the form of a participant information sheet) and verbally. The sheet will explain why the research is being conducted and what is involved in taking part. If the patient agrees to take part then informed consent will be gained and the patient will then be recruited into the trial. Patients will be informed that they can withdraw at any time without giving a reason. They will be assured that the decision to withdraw or to not take part will not affect the standard of care they receive. All additional relevant study information will be made available to participants on request (for example, copies of the research protocol). The process of recruitment and gaining informed consent has already been piloted in preliminary phases of this study and the research team are well versed in engaging and recruiting patients on hospital wards in a respectful and sensitive manner.

### Approvals process

NHS Research Ethics Committee approval was granted by South Yorkshire REC on 15^th^ March 2013 (13/YH/0077)NHS Research Governance approval for:Harrogate & District NHS Foundation Trust on 3^rd^May 2013Calderdale & Huddersfield NHS Foundation Trust on 17^th^ May 2013Leeds Teaching Hospitals NHS trust on 30^th^ May 2013International Standardised Randomised Controlled Trials Number from controlled-trials.com on 16^th^ August 2013

### Trial analysis

A full Statistical Analysis Plan will be written prior to any analyses. Analyses of individual level outcomes will account for clustering. For the primary outcomes, the difference between intervention groups will be estimated with 95% confidence intervals. The intervention groups will be compared with respect to the proportion of harm-free care across wards at 12 months. A linear regression model accounting for the minimisation factors and the baseline level of harm-free care will also be included as a covariate. As the outcome measure is on a ward level, no adjustment for clustering is required. The difference between the intervention groups at 12 months will be calculated with a 95% confidence interval. The standardised effect size will also be reported.

Multi-item PMOS domains will be treated as continuous data in the analysis. Linear mixed models accounting for the minimisation factors and baseline PMOS scores (ward level averages) will be used to compare the intervention groups with respect to each domain score at 12 months. Random effects will be used to account for the clustering at ward level. The difference in adjusted (least square) means will be summarised with 95% confidence intervals. Standardised effect size and ICC will also be calculated. Due to the nature of the intervention it is not possible to identify which domains are of primary interest, since the intervention across different wards may focus on improving different domains. Each domain will therefore be tested without adjustment for multiplicity. Interpretation of the *P* values will be considered carefully alongside the full details of which domain(s) the interventions in each ward were aiming to improve.

Secondary outcomes will be analysed using similar models to the primary outcomes. Ward level covariates will be added to the primary model in order to explore their influence. Continuous measures will be compared between groups using multi-level regression modelling accounting for trust/ward where required and the minimisation factors. Categorical measures will be compared between groups using logistic regression (or ordinal logistic regression for ordinal measures) adjusting for the Trust/ward where required and minimisation factors. The validity and reliability of the PMOS and domain scores will be investigated in this population using Cronbach’s alpha and known-group comparisons. All primary and secondary outcome measures will be summarised at each time point and by intervention group using summary tables or graphs/bar charts depending on the type of data.

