Wards will be randomly assigned to either the intervention or control groups, on a 1:1 ratio. Randomisation will be carried out by York Trials Unit Randomisation Service (based at the University of York) using a secure computer system. All wards from each Trust will be randomised in a batch. Although there is the possibility of staff moving between control and intervention wards in a hospital, the possibility of contamination between the groups is expected to be minimal. This is because the ‘Feedback Report’ is not available to control wards and the intervention is ward-specific dependent on this. Baseline data collection will be undertaken at least 1 month before randomisation to ensure completion of data collection before knowledge of randomisation. Once baseline data have been collected in a Trust, participating wards will be randomly allocated to one of the two arms: intervention or control. Minimisation will be used to balance the groups with respect to ward specialty, average age, single/mixed sex wards and ward size. After randomisation, ‘start up’ meetings will be held with intervention wards only. Intervention wards will be asked to set up action planning meetings in order to consider their first feedback report. The above process is detailed in flow chart format in Additional file
1: Appendix 4.

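### Trust is the randomisation batch but is missing from both primary models, so the primary intervals are probably somewhat wider than they need to be

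*Protocol article*

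**What the plan says.** **Allocation.** Setting and sample states: "All wards from each Trust will be randomised in a batch". The timing is also by Trust: "Once baseline data have been collected in a Trust, participating wards will be randomly allocated to one of the two arms". The balancing factors are given as: "Minimisation will be used to balance the groups with respect to ward specialty, average age, single/mixed sex wards and ward size". Trust is not among them. The 32 wards are listed as 8, 10 and 14, which I read as the counts for the three Trusts.

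**Timing.** Study period states: "We will stagger the start date for each trust, and for different wards in each participating trust". The Trusts therefore run in different calendar periods.

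**Primary models.** For harm-free care, Trial analysis specifies: "A linear regression model accounting for the minimisation factors and the baseline level of harm-free care will also be included as a covariate". The sentence is garbled, but the covariates are clear: minimisation factors and baseline. It continues: "As the outcome measure is on a ward level, no adjustment for clustering is required". The PMOS domain models name the minimisation factors, baseline ward averages and a random effect for ward.

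**Where Trust appears.** The following paragraph, which opens with the secondary outcomes, describes models for continuous measures "accounting for trust/ward where required and the minimisation factors", with similar wording for categorical measures.

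**The concern.** Each Trust is a self-contained randomisation batch. It also stands for a type of institution (from a small district general hospital to a very large teaching hospital) and for a calendar period. Adjusting for the minimisation factors does not bring Trust in.

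If each batch is split about evenly between the arms, the arm comparison is in effect made within Trusts. A model without Trust still charges the differences between Trusts to the residual. The standard error is then too large for the design, the interval too wide and the test conservative. With 16 wards per arm there is little precision to spare.

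The two paragraphs of Trial analysis also treat Trust differently without giving a reason.

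**Working it through.** **1. The plan's own figure.** Inputs from Estimate of sample size: effect 0.3 SD, power 80%, alpha 0.05 (taken as two-sided), 25 patients per ward, ICC 0.05.

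- Patients per arm without clustering: 2 × ((1.960 + 0.842)/0.3)² = 174.4, rounded up to 175.
- Design effect: 1 + 24 × 0.05 = 2.2.
- Wards per arm: 175 × 2.2 / 25 = 15.4, rounded up to 16, so 32 in total.

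The stated 32 wards are reproduced. Power at 16 per arm is 0.816 by the normal approximation and 0.79 by a t test on ward means with 30 degrees of freedom.

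**2. Batches balanced (4/4, 5/5, 7/7).** All three ward counts are even, so this split is possible, but the article does not promise it. Let s be the share of residual ward variance lying between Trusts. This is an assumption, because the article gives no value.

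With Trust in the model, the expected residual mean square is 1 − s on 28 df. With Trust omitted, there are 30 df. The Trust component adds to the residual sum of squares s × (32 − (8² + 10² + 14²)/32) = s × (32 − 11.25) = 20.75s. The expected mean square is therefore (30(1 − s) + 20.75s)/30 = 1 − 0.308s.

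Interval ratio, Trust included to omitted: √[(1 − s)/(1 − 0.308s)] × t(0.975, 28)/t(0.975, 30), where the last factor is 2.048/2.042 = 1.003.

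| Assumed s | Ratio | Change in width on adding Trust |
|---|---|---|
| 0 | 1.003 | 0.3% wider |
| 0.1 | √(0.900/0.969) × 1.003 = 0.967 | about 3% shorter |
| 0.2 | √(0.800/0.938) × 1.003 = 0.926 | about 7% shorter |
| 0.3 | √(0.700/0.908) × 1.003 = 0.881 | about 12% shorter |

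Simulations of the same layout without other covariates (10,000 and 20,000 runs) give 3%, 7% and 11-12%. With Trust omitted, the size of the nominal 5% test is 4.1-4.4%, 3.7-3.8% and 2.8-3.1%. With Trust included it is about 5.0%.

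A further simulation (6,000 runs per setting) added a baseline covariate with an assumed correlation of 0.5. The treatment effect was 0.3/√(0.05 + 0.95/25) = 1.01 ward-level SDs. There was no bias.

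| Assumed s | Coverage, Trust omitted | Power, Trust omitted | Power, Trust included |
|---|---|---|---|
| 0.1 | 95.8% | 0.895 | 0.909 |
| 0.2 | 96.0% | 0.907 | 0.933 |
| 0.4 | 97.6% | 0.943 | 0.979 |

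**3. Batches not balanced (1:1 overall only).** In the same simulation with Trust omitted, there was no bias and coverage was 94.8-95.5%. Mean interval widths:

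| Assumed s | Trust omitted | Trust included | Included / omitted |
|---|---|---|---|
| 0 | 1.268 | 1.317 | 1.04 |
| 0.05 | 1.252 | 1.278 | 1.02 |
| 0.1 | 1.242 | 1.248 | 1.00 |
| 0.2 | 1.221 | 1.178 | 0.96 |
| 0.4 | 1.165 | 1.018 | 0.87 |

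The gain from adding Trust therefore depends on near-balance within batches or on a share above about 10%.

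**4. PMOS.** Arm varies only between wards, and about 25 patients are recruited per ward. A mixed model with a ward random effect therefore behaves much like an analysis of ward means. The figures in step 2 carry over approximately, with s read as a share of the residual variance of ward means.

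**The case against.** The strongest defence is that this belongs to the statistical analysis plan. The article promises a full one before any analysis, does not say that Trust is excluded, and never calls Trust a stratification factor. The phrase about continuous measures is not expressly limited to secondary outcomes, so it might be meant to reach the primary models. This stands in part. But the article does list the covariates of both primary models and leaves Trust off, and names Trust one paragraph later. That is a stated choice or an ambiguity, not mere silence. The later mention is conditional and does not say whether Trust would be a fixed effect.

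The defence is also right that nothing here is anti-conservative. Three stronger readings are tempting, and the documents do not support them:

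- *The primary intervals ignore the randomisation structure.* They do not. All four minimisation factors and baseline are in the models, and only the batch is missing.
- *Trust is confounded with arm.* Allocation is random at 1:1, so any imbalance within a batch is chance. Step 3 shows no average bias and coverage near 95%.
- *The staggering of wards within a Trust contradicts the common window.* Setting and sample says "data collection occurs within the same 3- to 4-week window for all participating wards in the same Trust". Wards can start on different days inside one such window, since each stops at 25 patients. No contradiction is established, and nothing suggests that the arms would be measured in different months.

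**Conclusion.** The point holds as a matter of efficiency and clarity, not validity. Both primary models omit the group within which wards are randomised, which also carries most of the calendar-time difference. With roughly balanced batches, the consequence is conservative inference: intervals that Trust adjustment would shorten by about 3%, 7% or 11-12% at assumed shares of 10%, 20% or 30%. The true share is unknown and applies after baseline and the minimisation factors, which may already absorb part of the Trust difference. If batches are not balanced, the primary intervals remain valid on average and the gain is smaller, or slightly negative when the Trust share is low. The sample size is unaffected.

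**What to change.** In Trial analysis, name Trust (the randomisation batch) as a fixed effect in the harm-free care regression and in each PMOS mixed model. Reword the following paragraph so that it is clear which models include Trust and in what form. If Trust is to be left out of the primary models, give the reason. The choice should be fixed before any outcome data are analysed.

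The cost is 2 degrees of freedom out of 32 wards and a line or two of text. If Trust explains nothing, the interval widens by about 0.2-0.3% with balanced batches and by about 4% if allocation was balanced only overall. The real models also carry baseline and the minimisation factors, so fewer than 30 residual degrees of freedom are available and the loss of 2 weighs slightly more. As an illustration, going from an assumed 22 to 20 changes the t multiplier from 2.074 to 2.086, or 0.6%.
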